### 2.2. Selection of Subjects

#### 2.2.1. Participants and Eligibility Criteria

The study population will consist of patients after first-ever IS who will be enrolled within 5–10 days after stroke onset at the Comprehensive Stroke Centre at the University Hospital Olomouc according to the following inclusion criteria: (1) first episode of unilateral ischemic stroke is detected on magnetic resonance imaging (MRI), resulting in walking deficits; (2) NIHSS score of 1–12 points at the time of enrolment; (3) lower limb movement impairment, with a score of at least 1 point on the NIH Stroke Scale (NIHSS) at the time of enrolment; (4) dependency in walking according to the Functional Ambulatory Category (FAC), with a score in the interval <1,3> (supervision or assistance, or both, must be given when walking) at the time of enrolment; and (5) age between 18 and 80 years. The exclusion criteria will include: (1) a previous history of any stroke, either ischemic or hemorrhagic; (2) other diseases modifying or limiting walking ability, currently receiving rehabilitation, or participation in another study; (3) significant or symptomatic ischemic heart disease; (4) significant or symptomatic peripheral arterial disease; (5) obesity (BMI ≥ 40) or weight higher than 135 kg (the weight limit for the robot-assisted gait training); (6) sensory aphasia with the inability to understand (confirmed by a certified speech therapist); (7) moderate or severe depression present at the time of enrolment assessed using the Beck scale, with a score above 10; (8) known cognitive impairment; (9) previous disability or dependence in daily activities assessed using the modified Rankin Scale, with a score of ≥3; (10) currently receiving dialysis; (11) diagnosed and/or receiving treatment for cancer; and (12) the presence of other orthopedic or neurological conditions affecting the lower extremities. Standard exclusion criteria for MRI examination will also apply.

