#### 2.6.2. Secondary Outcomes

-Walking dependency

Walking dependency will be evaluated by the functional ambulation categories (FAC) using a 6-point scale ranging from 0 to 5. Scores in the interval <1,3> indicate a dependent ambulator who requires assistance from another person during walking (score 1—continuous manual contact, score 2—intermittent manual contact, and score 3—verbal supervision/guarding). Scores of 4 or 5 indicate an independent ambulator (score 4—independent walking on a level surface and score 5—independent walking on any surface). The FAC has been proven to have excellent reliability, good concurrent and predictive validity, and even good responsiveness in poststroke patients with hemiparesis [27]. The FAC scores have great potential to change significantly after the first 2 weeks of the early inpatient rehabilitation program [27].

-Brain activity related to gait recovery

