### 2.8. Randomization

The randomization of the enrolled participants for robot-assisted treadmill gait training (RTGT) or therapist-assisted treadmill gait training (TTGT) will be performed as a block randomization with a 1:1 allocation to either RRGT or TTGT. As mentioned above, in randomly selected IS patients with a 1:2 allocation, a repeated multimodal magnetic resonance imaging (MRI) examination, including functional MRI (fMRI), will be performed during the study follow-up.

Participants will be randomized after the screening of eligible participants by the certificated neurologist at the Comprehensive Stroke Centre and before the first clinical visit (visit 1).

Participants will be randomized in a 1:1 ratio and in a 1:2 ratio to multimodal magnetic resonance imaging (MRI) using the web randomization module. A randomized web number generator will be implemented for group allocation. Neurologists will generate the allocation sequences, enroll the participants, and assign the participants to interventions.

The allocation might be adaptively modified in cases when patients randomized for RTGT, after enrolment and during the course of rehabilitation, will be identified as independent walkers (FAC > 3). This change will be reported. It has previously been identified that stroke survivors with gait deficits (FAC ≤ 3) with higher motor impairment are those who benefit the most from robot-assisted therapy in combination with conventional therapy [15,23,47,48].

All participating patients will obtain a card before discharge (visit 2) with the dates of all scheduled outpatient events (visit 3 and visit 4), including the dates of the fMRI examinations and even the telephone contacts with the study investigators (neurologist and principal physiotherapist). All enrolled patients will be promoted and motivated to remain in the study and complete follow-ups during each scheduled visit. In participants who discontinue or deviate from the intervention protocols, the acquired outcome data will be collected for a further subanalysis.

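### The allocation of RTGT patients, and only RTGT patients, may be modified after randomisation when they reach FAC > 3, with no stated arm for their analysis

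*Protocol article*

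**What the plan says.** All from the protocol article.

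- **Section 2.8 (Randomization), the rule:** "The allocation might be adaptively modified in cases when patients randomized for RTGT, after enrolment and during the course of rehabilitation". The trigger is that such a patient is later "identified as independent walkers (FAC > 3"), and the only safeguard given is that the modification gets reported. The rule names RTGT only, and no section gives a counterpart for TTGT.
- **Section 2.8, timing:** randomisation takes place after screening "and before the first clinical visit (visit 1"). Table 1 puts allocation at visit 0.
- **Section 2.2.1 (Participants and Eligibility Criteria):** patients must be dependent walkers on the FAC, "with a score in the interval <1,3>", at enrolment.
- **Section 2.6.2 (Secondary Outcomes):** FAC is a secondary outcome. "Scores of 4 or 5 indicate an independent ambulator". The section adds: "The FAC scores have great potential to change significantly after the first 2 weeks of the early inpatient rehabilitation program".
- **Section 2.8, deviations:** outcome data of participants who discontinue or deviate are collected for a further subanalysis.
- **Section 2.5 (Study Protocol):** if the training intervention is discontinued for any reason, the participant need not attend the follow-up assessments.
- **Section 2.10 (Statistical Analysis):** RTGT is compared with TTGT. The section does not say whether membership is as randomised or as later modified.

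**The concern.** A randomised comparison is protected by the fact that nothing occurring after randomisation decides which arm a patient counts in. The sentence in section 2.8 sets that protection aside. It acts in one arm only, and it is triggered by good recovery. What it modifies is the allocation, not merely the training delivered. It is also discretionary, because the word *might* leaves open which qualifying patients are changed. Reporting the change, the only safeguard given, does not undo its effect on the comparison.

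Patients who reach FAC > 3 early will tend to be the faster walkers. If RTGT loses them, its mean gait speed falls. If TTGT also gains them, its mean rises. Either way the trial could conclude against RTGT when the two trainings are equally good, or miss a real RTGT benefit.

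**Working it through.** **Inputs from the article.** Section 2.7: 60 per arm, 85% power, alpha 5%, target 0.16 m/s, 15% missing data and 10% loss to follow-up. Section 2.2.1: FAC 1 to 3 at entry.

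**Assumptions, because the article gives no figure.** Two-sided test; losses multiply; share x of RTGT patients whose allocation is modified = 10%, 20% or 30%; movers walk g = 0.25 m/s faster than the other RTGT patients; no true difference between the trainings.

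**Step 1: the plan's own figure.** No SD is stated, so the total of 120 cannot be reproduced independently. Working backwards, evaluable patients per arm = 60 × 0.85 × 0.90 = 45.9, about 46. For 85% power, 0.16 / (SD × √(2/46)) = 1.960 + 1.036 = 2.996, so SD ≈ 0.256 m/s. I use the rounded value 0.25. With SD 0.25 the requirement is 44 per arm, or 58 to 59 after inflation, which fits 60.

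**Step 2: bias.** Set the mean of each randomised arm to 0. Movers then average (1 - x)g and the remaining RTGT patients average -xg.

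- *Dropped:* RTGT - TTGT = -xg.
- *Counted in TTGT:* the TTGT mean becomes x(1 - x)g/(1 + x), so RTGT - TTGT = -xg - x(1 - x)g/(1 + x) = -2xg/(1 + x).

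**Step 3: false-positive rate.** With N = 46, SE = 0.25 × √(1/(N - xN) + 1/(N + xN)) if movers are counted in TTGT, and 0.25 × √(1/(N - xN) + 1/N) if they are dropped. The rate is Φ(|bias|/SE - 1.96) + Φ(-|bias|/SE - 1.96).

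Worked case, x = 20%, counted in TTGT: bias = -2 × 0.2 × 0.25/1.2 = -0.083. SE = 0.25 × √(1/36.8 + 1/55.2) = 0.0532. Ratio 1.57. Rate ≈ Φ(-0.39) ≈ 0.35.

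| Share moved | Counted in TTGT: bias (m/s) | % of 0.16 | False positives | Dropped: bias (m/s) | % of 0.16 | False positives |
|---|---|---|---|---|---|---|
| 10% | -0.045 | 28% | 14% | -0.025 | 16% | 7.5% |
| 20% | -0.083 | 52% | 35% | -0.050 | 31% | 15% |
| 30% | -0.115 | 72% | 56% | -0.075 | 47% | 26% |

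**Step 4: sensitivity.** At 20% counted in TTGT, a gap of 0.15 to 0.35 m/s gives a bias of -0.05 to -0.12 m/s. A simulation under a different model (8,000 trials per setting, SD 0.256, early recovery correlated 0.3 to 0.7 with gait speed) agrees in direction and scale. At 20% moved, the false-positive rate is 13% to 48% if movers are counted in TTGT and 8% to 21% if dropped. With a true RTGT benefit of 0.16 m/s that movers keep in full, and correlation 0.5, the estimate falls to about 0.06 m/s with power 17% (counted in TTGT), or 0.115 m/s with power 54% (dropped).

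**Step 5: analysed as randomised.** Bias is 0 and the false-positive rate about 5%. If movers lose all of the RTGT effect, the 0.16 m/s difference shrinks by the factor (1 - x), and power = Φ(2.996(1 - x) - 1.96): about 77%, 67% and 55% at 10%, 20% and 30%. The comparison is diluted but valid.

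**The case against.** The strongest reply is that the sentence is permissive and incomplete. It does not send patients to TTGT, since they might simply stop assisted training, and it does not say how they are analysed. A statistical analysis plan not shown here could analyse everyone as randomised, and an article commonly leaves analysis sets to that plan.

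Much of this stands, and it limits four inferences that a reader might draw:

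- *That the rule destroys the randomised comparison.* This follows only if patients are analysed by modified allocation or removed. The article fixes neither.
- *That the trigger will be common.* Section 2.6.2 says FAC may well change within two weeks, but a move from 1 to 2 is also a change. No section says how many patients will pass 3.
- *That deviating patients leave the main analysis.* Section 2.8 says their data are collected for a further subanalysis. It does not exclude them elsewhere, nor does it say that a change made under the protocol's own rule counts as a deviation.
- *That the visit 1 baseline is compromised by unblinded patients.* Allocation does precede visit 1, but visit 1 precedes the training programme, assessors are blinded (section 2.4), and the article does not say when patients learn their arm.

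What does not stand is the appeal to the unseen plan as a full answer. The point rests on a stated rule that modifies allocation, not on a missing detail. An as-randomised analysis would have to override that rule. It would also need follow-up data that section 2.5 does not require once training is discontinued.

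**Conclusion.** The concern holds in this form: section 2.8 permits a one-arm, response-triggered change of allocation after randomisation, and names neither the destination nor the analysed arm. Any analysis that follows the modified allocation, or removes these patients, is biased against RTGT. The direction needs only that patients reaching FAC > 3 walk faster on average than the other RTGT patients. The size rests on the assumed share moved, the assumed speed gap and the back-solved SD, so the table in the working is an illustration, not a forecast. At 20% moved the bias is about one third (dropped) to one half (counted in TTGT) of the 0.16 m/s target. Because this touches the trial's only randomised contrast on its primary outcome, and outcomes never collected cannot be recovered later, the text should be changed.

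**What to change.** 1. **Section 2.8.** Replace the sentence on modifying the allocation with: *The randomised allocation is never changed; every randomised patient is analysed in the arm to which he or she was randomised, and any change of training in either arm is recorded and reported by arm.* Whether a patient's training changes at FAC > 3 remains a clinical decision, on which this point takes no position.
2. **Section 2.5.** Amend the follow-up sentence so that patients whose training is changed or discontinued are still invited to all follow-up assessments.
3. **Section 2.8.** State that the further subanalysis of patients who discontinue or deviate is additional to their inclusion in the main analysis.

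The cost is protocol wording and follow-up visits for patients who might otherwise not attend. The downside to declare is dilution: in the worst case of 20% fully switched, power falls from 85% to about 67%.

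A separate and lesser suggestion is to randomise to RTGT or TTGT after the visit 1 assessments and before the first training session, so that baseline precedes allocation. This needs coordination, because randomisation sits with the neurologists at the Stroke Centre and training with the Department of Rehabilitation. It does not by itself deal with patients who pass FAC 3 between enrolment and visit 1, and it does not replace items 1 to 3.

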### 2.9. Data Management

The study protocol, data collection forms, and even files with outcome data will be stored on a locked disc shared with study investigators, and every 3 months all data will be backed up on external discs. All collected patient data will be shared and analyzed anonymously. All questionnaires and clinical scales of all participants will be stored for further analysis. All patient data will be scrambled to ensure confidentiality.

Personal information about potential and enrolled participants will be collected by only one investigator without further sharing within the study team. Patients´ personal information will be confidential to all other study investigators during the study duration as well as after the end of the trial. All collected patient data will be shared and analyzed strictly anonymously.

All reported adverse events or other unintended effects of the trial interventions will be recorded. Missing data for each variable will be reported.

There are no plans to give access to the full protocol, the participant-level data, or the statistical code.

### 2.10. Statistical Analysis

For the statistical analysis of all tested clinical parameters, gait movement pattern parameters, and extracted imaging parameters, the distribution of the data will first be explored. If normally distributed, a two-factor mixed-model ANOVA will explore the differences between the groups and time points. If not normally distributed, Friedman tests will be used to explore the differences between time points (visits 1–4) within each group and Mann–Whitney U tests will be used to explore the differences between both groups (RTGT and TTGT).

The statistical analysis of fMRI data will include standard preprocessing with subsequent general linear model fitting and a group-wise analysis in the Montreal Neurological Institute (MNI) 152 standard space after the nonlinear normalization of the individual structural MRI data [49]. Significant group effects will be evaluated using an analysis of covariance (ANCOVA) with group, visit, and age as covariates. An atlas-based region of interest (ROI) analysis will be used to evaluate the amplitude and volume of the primary sensorimotor and premotor activations and the laterality index (ipsilesional − contralesional/ipsilesional + contralesional), which are the main secondary outcome measures of the fMRI analysis. Since the functional study design and paradigm partly follow the study of Boyne et al. [32], the choice of regressors and contrasts for the statistical analysis of the corresponding data will likewise follow that study. Structural data (DWI and T1-weighted) will be evaluated in separate pipelines to extract the following parameters from anatomically defined ROIs: regional cortical thickness; fractional anisotropy (FA); and axial, radial, and mean diffusivity (AD, RD, and MD), respectively. Alternative DWI analysis models may include, e.g., FD/FDC or NODDI. The quantitative parameters derived from functional and structural imaging will be included in an extended factor analysis of the global predictors of gait recovery.

With respect to the type of missing variable, the appropriate imputation (e.g., single imputation, multiple imputation, etc.) might be performed if needed [50].

As data accumulate, the validity and the integrity of the trial will be subjected to an interim analysis after the first 30 participants have been assessed at all four timepoints. The interim analysis, including the first 30 completely measured participants, will guide the final statistical methods. An interim analysis based on 30 participants with complete data will be conducted to perform a power analysis and to compute the final sample size. The principal investigator will have access to the interim results. Additional analyses and further subgroupings are not planned.

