Specific brain structures with possible impacts on gait recovery in IS patients will be identified using functional magnetic resonance imaging (fMRI) during simple lower limb movements, gait imagery, and gait observation as well as using diffusion-weighted imaging (DWI) and surface-based morphometry. The functional MRI activation magnitude, calculated as the difference in the BOLD signal between task and rest, will be assessed within predefined gait-related brain regions of interest (ROIs), i.e., the sensorimotor cortex, premotor cortex, supplementary motor area, brainstem, and cerebellum. Changes in these ROI parameters over time will be statistically tested within the group, and the regional post-training minus pretraining difference in each group will be submitted to a between-group analysis. Gait recovery after treadmill exercise has been associated with increased task-related activation in the posterior cerebellum and brainstem [28] as well as in the primary sensorimotor cortices and basal ganglia [29]. Moreover, the task-related activation volume in the ipsilesional primary sensorimotor foot representation has been identified as an independent baseline predictor of gait recovery [30]. However, simple leg movements may not be sufficiently representative of a more complex motor behavior such as gait. As it is impossible to directly measure gait-related brain activation in fMRI, gait imagery has been employed as a substitute for real movements in healthy subjects [31] as well as stroke patients with gait impairment [32]. Beyond fMRI, other potential imaging biomarkers include white matter integrity, assessed using diffusion-weighted imaging (DWI), and surface-based morphometry based on structural imaging [33]. So far, according to systematic reviews, evidence for biomarkers based on fMRI, DWI, and structural MRI data remains inconclusive, mostly due to methodological limitations [16].

-Neurological impairment

The National Institute of Health Stroke Scale (NIHSS) represents the most widely used rating scale to evaluate neurological impairment after IS [34]. The NIHSS includes items on consciousness, language, movement, sensation, ataxia, eye movement, the visual field, and others. The scores range from 0 to 42, with higher scores indicating more severe neurological deficits.

-Sensorimotor impairment

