### 2.7. Sample Size

Based on an analysis of our pilot data concerning the gait velocity (primary outcome), 120 participants (60 in each group) are anticipated to be enrolled in this study. This number of participants would provide 85% power (α level 5%) to detect a difference of 0.16 m/s in the 10 MWT (with respect to a missing data rate of 15% and an expected 10% drop in the follow-ups) between groups after intensive rehabilitation with add-on intervention. The gait speed difference of over 0.16 m/s was previously defined as the minimal clinically important difference in gait speed in subacute stroke patients [46].

For the multimodal magnetic resonance imaging (MRI), including functional MRI (fMRI), we have estimated that a sample size of 50 participants (25 in each group) will suffice to find significant correlations of MRI outcomes with gait recovery. This is based on previous studies of fMRI and gait recovery in similar clinical cohorts [29,32]. We will perform multimodal MRI in half of the randomly selected enrolled IS patients (1:2 randomization), i.e., in 60 participants, to allow for a common drop-out of examined patients with MR images of poor or insufficient quality. As we do not have sufficient information to estimate the variance in the outcomes, we plan to calculate the definitive effect sizes based on the interim analysis of the first 30 subjects measured within all four visits (visit 1–visit 4).

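### The fMRI region-of-interest measures are given two or three different between-arm analyses and none is named as deciding, so the per-measure false-positive rate could be about 8–15% rather than 5%

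*Protocol article*

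**What the plan says.** Three places in the protocol article bear on how the arms are compared on fMRI.

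- **Section 2.10, first paragraph.** The general rule covers "all tested clinical parameters, gait movement pattern parameters, and extracted imaging parameters, the distribution of the data will first be explored". If the data are normal, "a two-factor mixed-model ANOVA will explore the differences between the groups and time points". If not, Friedman tests are used within arms and Mann–Whitney tests between arms, with no visit named.
- **Section 2.10, second paragraph, on fMRI data.** "Significant group effects will be evaluated using an analysis of covariance (ANCOVA) with group, visit, and age as covariates". This follows a sentence on group-wise analysis in standard brain space. The next sentence introduces the ROI amplitude, volume and laterality index, "which are the main secondary outcome measures of the fMRI analysis".
- **Section 2.6.2, brain activity.** Changes in the ROI parameters are tested within arms, and "the regional post-training minus pretraining difference in each group will be submitted to a between-group analysis".

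Main fMRI measures are therefore named, but no main test. The last paragraph of section 2.10 adds that the interim analysis of the first 30 completed participants will guide the final statistical methods, and that the principal investigator will have access to the interim results.

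**The concern.** The prescribed analyses ask different questions. The ANOVA interaction asks whether the arms differ in their profile over visits 1–4. The ANOVA group effect and the ANCOVA group term ask about an average over visits. The post-minus-pre comparison isolates the training period, which by the visit schedule in section 2.5 runs from visit 1 to visit 2. They can disagree on the same data, and each could fairly be described as planned. If the significant one is reported as the arm effect, the 5% error rate no longer holds for that measure. This is a matter of competing instructions already in the text, not of detail left to a later document. The provision that interim data may guide the methods means that the choice could be made after data have been seen.

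**Working it through.** **Plan's own figure.** No error rate is stated for the fMRI comparisons. The only stated level belongs to gait speed ("85% power (α level 5%) to detect a difference of 0.16 m/s in the 10 MWT"). I assume two-sided 5% for each fMRI test. The MRI sample was sized for something other than an arm comparison: "a sample size of 50 participants (25 in each group) will suffice to find significant correlations of MRI outcomes with gait recovery".

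**Inputs.** From the article: 25 evaluable participants per arm (30 per arm if all 60 are usable) and four visits. Assumed, because section 2.7 says the variance is not known: standardised data, between-visit correlation ρ of 0.3–0.8, and an age effect of 0 or 0.5 SD per SD of age. The ANCOVA is given a participant-level error term so that each test is valid alone. The post-minus-pre difference is taken as visit 2 minus visit 1.

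**Step 1: the estimands.** Let δk be the RTGT–TTGT difference at visit k.

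- ANOVA interaction: are δ1 to δ4 all equal?
- ANOVA group effect, or ANCOVA group term: is (δ1+δ2+δ3+δ4)/4 = 0?
- Post-minus-pre: is δ2 − δ1 = 0?

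**Step 2: error rate if any significant test may be reported, no true difference.** Each test alone simulates at about 5% (3–6%). Independent benchmarks: 1 − 0.95² = 9.75% for two tests and 1 − 0.95³ = 14.3% for three.

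| Tests available for one measure | At least one p < 0.05 |
|---|---|
| Interaction + post-minus-pre (ANCOVA read as map-level) | 7.6–8.4% |
| Group effect + ANCOVA + post-minus-pre, no age effect | 9.6–10.9% |
| The same, with an age effect | 11.4–12.4% |
| Interaction + ANCOVA + post-minus-pre | 10.8–13.8% |
| Mann–Whitney at visit 2 + ANCOVA + post-minus-pre | 11.2–12.5% |
| Group effect and interaction + ANCOVA + post-minus-pre | 11.4–15.4% |

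If the two-test reading uses the ANOVA group effect instead of the interaction, the rate is close to 9.75%. With equal variances and equal correlations, the average over visits and the visit 2 minus visit 1 change have zero covariance, so the two tests are nearly independent.

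**Step 3: how far the tests can diverge (ρ = 0.6, 25 per arm).** The standard error of an arm difference is SD × √(2/25) = 0.283 × SD, and the t cut-off is about 2.01.

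- *Change:* SD = √(2(1 − 0.6)) = 0.894, SE = 0.253. For δ2 − δ1 = 0.8 SD, 0.8/0.253 = 3.16, so power ≈ Φ(3.16 − 2.01) = Φ(1.15) ≈ 87%.
- *Average over visits, effect at visit 2 only:* the average is 0.8/4 = 0.2, SD = √((1 + 3×0.6)/4) = 0.837, SE = 0.237. Then 0.2/0.237 = 0.85, and power is about 12–13%.
- *Average over visits, effect lasting over visits 2–4:* the average is 0.6, 0.6/0.237 = 2.54, and power ≈ Φ(0.53) ≈ 70%.
- *Interaction:* 91% by simulation in both scenarios.

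**Step 4: a single contrast as replacement.** For visit 2 adjusted for visit 1, the residual SD is √(1 − ρ²).

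- ρ = 0.6: SD 0.8, SE 0.226, ratio 3.54, power about 93%, against 87% for the change test.
- ρ = 0.4: SD 0.917, SE 0.259, ratio 3.09, power about 85%, against 72% for the change test.

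Simulated error for this contrast alone is about 5%.

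**The case against.** The best defence is that the texts can be reconciled. The ANCOVA sentence comes straight after the standard-space group analysis and before the ROI sentence, so it may concern maps only. Section 2.6.2 names no method for the post-minus-pre comparison, and that comparison can be read as a contrast within the mixed ANOVA or as the input to a Mann–Whitney test. Choosing one deciding contrast for a secondary imaging outcome is also commonly left to the analysis plan.

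Much of this stands. The count is two or three, not certainly three. But even on the two-test reading, the four-visit ANOVA and the training-period change are different comparisons, and nothing says how they relate. An analysis plan can fill a gap, but here competing instructions are already written down.

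A reader might infer several stronger points that the article does not support:

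- **That the error rate more than doubles whatever is done.** Any single test fixed in advance keeps about 5%. The two-test figure of about 8% is not a doubling, and the mildest three-test reading only about doubles it. The article does not say that one significant test suffices.
- **That all imaging parameters are affected.** Cortical thickness and the diffusion measures receive only the general rule.
- **That the tests usually contradict each other.** With an effect at visit 2 only, the three verdicts differ in 84% of simulated trials, but that is the worst case for an average over visits. If the effect persists, the figure is about 40%, and the interaction and change tests alone differ in about 10%.
- **That the ANCOVA treats repeated visits as independent.** That would give 15–28% error by itself. The article does not mention a within-participant term, but does not exclude one.

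**Conclusion.** The point holds for the fMRI ROI amplitude, volume and laterality index. Two or three between-arm analyses with different estimands are prescribed, none is named as deciding, and the choice is open to influence from interim data. If any significant result may be reported as the planned effect, the per-measure false-positive rate is roughly 8% with two tests (nearer 10% if the ANOVA group effect is the term used) and 10–15% with three. These figures rest on assumed correlations, two-sided 5% tests and an ANCOVA that respects repeated visits. Only secondary fMRI conclusions are at stake; the gait-speed conclusion is untouched. The text should be corrected, but the trial's main result does not depend on it.

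**What to change.** Before the interim look:

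1. For each main fMRI ROI measure, name one deciding contrast: the RTGT–TTGT difference at visit 2 from a participant-level model with the visit 1 value as covariate. This answers the post-versus-pre question in section 2.6.2.
2. For these measures, label the mixed ANOVA or Mann–Whitney tests, the ANCOVA and the later visits as supportive.
3. State whether the ANCOVA is for voxel-wise maps only.
4. Keep the general rule in section 2.10 for the structural MRI parameters. Removing imaging parameters from it altogether would leave them with no stated between-arm test.

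The cost is wording only, with no new data. In the settings checked, power is at least that of the change test. The small downside is that an effect appearing only at visits 3–4 would count as supportive evidence.
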